# Prevention of sick leave at the workplace: design of a cluster-randomized controlled trial of a problem-solving intervention among employees with common mental disorders

**DOI:** 10.1186/s12889-021-11786-6

**Published:** 2021-09-26

**Keywords:** Adjustment disorder, Anxiety disorder, Blue-collar worker, Cluster-randomized controlled trial, Common mental disorder, Depression, Manager, Prevention, Problem solving, Sick leave

## Abstract

**Background:**

Common mental disorders are highly prevalent in the working population, affecting about 1 in 5 persons in the Organisation for Economic Co-operation and Development countries. About 30% of those affected have a first period of sick leave. Despite several attempts to reduce the risk of sick leave among employees with common mental disorders, there is a lack of knowledge about effective, preventive interventions which aim to reduce such risks. This protocol describes the design of a study to evaluate the effectiveness of a problem-solving intervention delivered by first-line managers to employees with common mental disorders on the prevention of sick leave during the 12-month follow-up.

**Methods/design:**

The study applies a two-armed cluster-randomized trial design of a problem-solving intervention conducted in private-sector companies. First-line managers are randomized into intervention- or control groups by computer-generated random numbers, allocation ratio 1:1. Employees are eligible if at risk for future sick leave due to common mental disorders. These are identified by self-reported psychological health measured by the General Health Questionnaire 12-item, cut-off ≥3, or a positive answer to risk of sick leave.

The intervention is based on problem-solving principles. It involves the training of the first-line managers who then deliver the intervention to employees identified at risk of sick leave. First-line managers in the control group receives a lecture. Primary outcome is number of registered days of sick leave due to common mental disorders during the 12-month follow-up. Secondary outcomes are general health, psychological symptoms, work performance, work ability and psychosocial work environment. A process evaluation will examine the intervention’s reach, fidelity, dose delivered, dose received, satisfaction and context. Research assistants managing the screening procedure, outcome assessors and employees are blinded to randomization and allocation.

**Discussion:**

The study includes analyses of the intervention’s effectiveness and an alongside process evaluation. Methodological strengths and limitations, for example the risk of selection bias, attrition and risk of contamination are discussed.

**Trial registration:**

Clinicaltrials.gov NCT04975750 Date of registration: 08/16/2021.

## Background

Common mental disorders (CMD), i.e. depression, anxiety, adjustment disorders and stress-related mental disorders, are highly prevalent in the working population and have been estimated to affect about 1 in 5 persons in countries belonging to the Organisation for Economic Co-operation and Development (OECD) [1, 2]. CMDs have major consequences, affecting individuals and the society at large [3]. CMDs cause individual suffering and pose a risk of social isolation, stigmatization, and long-term sick leave [4]. In the European Union, the estimated annual costs related to mental ill-health were more than 600 billion Euros in 2015, including costs for health care systems, social security programs and indirect costs (i.e. sick leave and impaired work performance) [2].

For employees in general, and specifically for those suffering from CMDs, having paid employment is beneficial for their health [5–8]. Modini et al. identify several individual benefits of employment compared to unemployment. These include increased sense of autonomy, improved self-reported well-being, reduced depression and anxiety symptoms, increased ability to cope with demands, enhanced social status, and unique opportunities for personal development and mental health promotion [5]. The vast majority of individuals with CMDs is employed and about 30% of these employees have a first period of sick leave due to CMDs during adulthood. Around 20–30% of the 30% of employees with a first sick leave spell have recurrent sick leave episodes [9]. Hence, the total burden of sick leave (e.g. individual suffering, isolation, economic loss and societal costs) and the individual benefits of employment emphasize the importance of sick leave prevention.

The current protocol reports the design of a cluster-randomized controlled trial of measures to prevent sick leave. It is based on an effective intervention carried out in the Netherlands by Lexis et al. [10]. The authors evaluated a problem-solving intervention among employees with high risk of sick leave due to depression. The intervention was delivered by specially trained psychologists and was found to prevent future long-term sick leave, defined as more than 28 consecutive days, and to reduce depression [10]. The results indicate the preventive potential of the problem-solving intervention, in particular with regard to long-term sick leave. Given the knowledge that a first period of sick leave can be followed by recurrent spells of sick leave, there is still a need of develop and evaluate interventions which aim to prevent the risk of entering sick leave in the first place.

Several randomized controlled trials evaluating the effectiveness of workplace interventions have been conducted among employees with CMDs or mental health symptoms. Their aim has been to decrease the number of sick leave days [11], prevent long-term sick leave [10], increase return-to-work (RTW) [12], or prevent work disability [13]. Some positive results have been reported, even if the long-term effects of workplace interventions for sustainable RTW are still unclear [11, 12]. One such intervention is a problem-solving intervention based on the principles of cognitive behavioral therapy (CBT) [11]. Evaluations of the effectiveness have shown some positive results in terms of reducing sick leave [14], preventing recurrent sick leave [15], preventing future long-term sick leave, reducing depression [10] and increasing partial RTW [16]. Another workplace intervention is the participatory approach (PA), which is a stepwise intervention involving managers and employees aimed to identify and implement solutions for RTW [17]. The PA has been shown to reduce time until lasting RTW has been achieved among those employees whose baseline measurement indicated an intention to RTW despite having symptoms [18]. In addition, the PA has been evaluated regarding the intervention’s impact on managers’ self-efficacy in preventing sick leave among their employees. It did not, however, result in a reduction of sick-listed employees or sick-leave duration [19].

Workplace interventions at the individual level – irrespective of whether they target employees who are at risk of or already on sick leave – often involve the employee, the employer and a health care or occupational health service professional. Typically, these interventions support the employee in identifying and managing stressors, or in dealing with barriers to RTW, thus placing the responsibility on the individual to adapt to the current situation [20, 21]. There is ample evidence that the psychosocial work environment - such as experiencing fair treatment and having influence over one’s work - is vital for the employees’ mental wellbeing [22, 23]. In the current study, the problem-solving intervention is used as a means to identify and manage adverse psychosocial work environment factors and to enhance the influence over their work situation [12, 22].

Hence, by applying a structured problem-solving process, addressed in stepwise meetings between the first-line manager and their employee, the problem-solving intervention is expected to reduce the risk of sick leave among employees with early signs of CMDs.

The overall aim of this cluster-randomized controlled trial is to evaluate the effectiveness of a problem-solving intervention for the prevention of sick leave among employees with early signs of CMDs. The intervention is delivered by first-line managers and a 30% reduction in sick leave days is expected in the experimental condition compared to the control condition, during the 12-month follow-up. In an alongside process evaluation on the intervention’s core activities, i.e. identification of early signs of CMDs, information to first-line managers about worker health and early signs of CMDs, training of first-line managers in problem-solving conversation and communication, we will:
evaluate to what extent it was possible for the first-line managers to adhere to the intervention’s protocol,investigate the association between the intervention’s core activities and number of sick leave days,identify the facilitators or and barriers to the intervention among first-line managers and employees and,explore the first-line manager’s organizational resources supporting their general managerial work.

The process evaluation will provide in-depth knowledge and insights into the intervention’s mechanisms and will make it possible to identify determinants of an effective intervention implementation and of change mechanisms. The study will be conducted in private sector companies among first-line managers and blue-collar workers. The outcomes will be evaluated at both cluster- and individual participant level.

## Methods/design

The study applies a two-armed cluster-randomized controlled trial design of a problem-solving intervention to prevent sick leave among occupationally active, blue-collar employees with CMDs (Fig. 1). The description of the study design follows the CONSORT statement for randomized controlled trials, with extension to cluster randomized controlled trials [24, 25]. The trial involves a psychologist training of first-line managers to deliver the intervention, developed in the Netherlands [10] and adapted to the Swedish context. First-line managers are commonly the first ones to identify employees with a reduced work performance or who are at risk for sick leave due to health complaints. This is also in line with the PA intervention with a stepwise protocol for meetings between manager and employee [17].

**Fig. 1 Fig1:**
[figure not shown]
Flowchart and overview of the trial

The study will take place at several private companies. Randomization will take place at the level of the first-line managers, i.e. those with personnel responsibility. The employees will follow their first-line manager’s randomization. The employees will have access to the occupational health services (funded by each company) or primary health care (publicly funded), if the screening identifies severe conditions that necessitate care by medical professionals.

The trial’s program theory with expected changes and outcomes is presented in a logic model (Fig. 2).

**Fig. 2 Fig2:**
[figure not shown]
The problem-solving intervention’s program theory with the intervention’s core activities, expected changes and outcomes on organizational and individual levels

### Context

In Sweden, individuals above the age of 16 who cannot work due to disease or injury are entitled to full or part-time sick leave (25, 50, 75 or 100%). Those who are gainfully employed receive economic compensation from their employer for the first 14 days, except for one qualification day. Thereafter, the Swedish Social Insurance Agency (SSIA) grants the benefits. The Swedish social insurance system is mainly tax funded. To receive economic compensation for sick leave, a sickness certificate issued by a physician is needed from day 8.

### Participants

#### Recruitment of first-line managers

Information about the study’s aim and design is provided to the steering groups at each company by the principal investigator ([name]).

##### Inclusion criteria

Eligible first-line managers are included if they meet the following criteria:
≥1-year work experience as a first-line managerWorking hours ≥50% of fulltimeUnderstand written and spoken Swedish

##### Exclusion criteria

Planned long-term absence during the coming year (for example parental leave, new job, retirement)

#### Recruitment of employees

To be eligible for participation an employee must be at risk for future sick leave due to CMDs. Employees at risk are identified by a web-based screening questionnaire, administrated by a research assistant to all employees whose first-line managers have been included and randomized. The following health and sick leave measures will be screened by the web-based questionnaire;

Self-reported psychological health is measured by the validated General Health Questionnaire (GHQ) 12-item, Swedish version [26]. The items include aspects reflecting different symptoms primarily related to depression but also general anxiety symptoms, for example stress, and further ability to perform daily activities and coping with everyday problems. Six items are positively worded and six items negatively. The time period assessed is the past few weeks. Every item has a four-category response format, namely “better than usual”, “same as usual”, “less than usual” and “much less than usual” [26, 27]. The traditional scoring method (all items are coded 0–0–1-1) will be used. Individuals scoring ≥3 are categorized as at risk for sick leave due to CMDs. This cut-off has previously been used in the Swedish Public Health Agency’s national surveys [28].

Sick leave risk is measured by a single question, developed by the research group: “About your health – do you think you will receive sick leave benefits because of stress, anxiety or depression in the coming 12 months?”. The response format is a 4-point scale, ranging from “Yes, most likely”, “yes, quite likely”, “I’m not sure”, “no, probably not”. The employee’s own beliefs and/or expectations about future sick leave have been shown to predict sick leave [4, 29].

#### Eligibility criteria

##### Inclusion criteria

Employees will be included if they meet the following criteria:
women and men, employed in the private sector, aged 18–59 years,scoring with a cut-off ≥3 points on the GHQ-12, or a positive answer (i.e. “yes, most likely”, “yes, quite likely”) on the question on sick leave risk,understand written and spoken Swedish.

##### Exclusion criteria

Ongoing sick leave (full- or part-time), leave of absence, pregnancy,sick leave ≥14 calendar days during the last 3 months due to CMDexposed to workplace bullying by the first-line managerplanned long-term absence during the coming year (for example parental leave, new job, retirement).

The research assistant screens the incoming answers on the web-based screening questionnaire for inclusion and exclusion criteria. Those who meet the inclusion criteria are informed by the research assistant (via e-mail or a telephone call) about their screening result and are recommended to talk to their first-line managers. Eligible employees follow the randomization of their first-line manager. The research assistant is blinded to group allocation.

### Randomization and blinding

The current study is designed as a two-armed cluster-randomized controlled trial. The randomization of participants is computer-generated, stratified by company, and takes place at the level of first-line managers. They are allocated at the individual level to intervention- or control group by means of computer-generated random numbers with allocation ratio 1:1. The random allocation sequence is generated by an independent statistician. The first-line managers will be enrolled and informed about their allocation by a research assistant.

To avoid contamination, the first-line managers in the intervention arm are instructed to talk and discuss the intervention only with each other and the project team. The first-line managers are not blinded to allocation since they will know about their participation in the problem-solving training (intervention) or the workshop (control condition).

Eligible employees follow the randomization of their first-line manager and are randomized before providing informed consent. All employees, irrespective of whether they are in the intervention- or control group, receive the same information about the study. The information contains details about randomization but not about the content of the two arms, i.e. the employees are blinded for their group allocation. Research assistants, blinded to the first-line managers’ and employees’ randomization, will manage the screening procedure and the outcome assessments (i.e. administration of baseline, follow-up questionnaires and text messages). The statistical analyses will be performed by an independent statistician who will be blinded for the participants’ randomization (both first-line managers and employee).

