### Strengths and limitations

The current study has some important strengths. To start with, a cluster-randomized controlled trial design will be used when evaluating the effectiveness of the problem-solving intervention on the primary outcome, i.e. register-based days of sick leave. The trial will be conducted at several workplaces; these are settings in which there are limited opportunities to conduct a rigorous randomized controlled trial. The cluster-design will allow the first-line managers to provide either the problem-solving intervention or the control condition. The first-line managers in the intervention group will also be told not discuss the intervention with their colleagues outside the intervention group. An additional strength is the use of register data for measuring the primary outcome. The data from the employer’s register and MiDAS will provide objective data about sick leave from day one, and we expect no missing data.

Another strength is the recruitment procedure. We will use a screening procedure to identify employees with early signs of CMD and at risk of future sick leave due to CMDs. Research assistants will screen the incoming answers and administer the baseline measurement to those meeting the inclusion criteria. The assistants have no previous knowledge about the employees and are blinded to group allocation. By using this procedure, we can reduce the risk of selection bias.

We must also mention some limitations. The screening of employees’ risk of future sick leave due to CMDs will be carried out among all employees whose first-line manager participates in the study. There is a potential risk that only employees who have confidence in and a trustful relationship with their first-line manager will respond to the questionnaire, implying that largely motivated employees or employees who only have minor problems will be included in the study. This may affect the generalizability of the study. However, participation is voluntary for both first-line managers and employees. Another limitation is the data collection, with self-reported questionnaires administered at baseline and at 6- and 12-month follow-up, and text messages sent every fourth week during the 12-month follow-up. We cannot rule out the risks of recall bias. However, we suggest that the response burden is appropriate.

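### Employees are screened, excluded and consented after their unblinded manager is randomised, so recruitment could differ by arm; the article treats the resulting selection only as a generalisability issue

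*Protocol article*

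**What the plan says.** The order of events is in two sections of the protocol article. Under Recruitment of employees, the screening questionnaire is "administrated by a research assistant to all employees whose first-line managers have been included and randomized". Under Randomization and blinding, "Eligible employees follow the randomization of their first-line manager and are randomized before providing informed consent".

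The same section says of managers that "The first-line managers will be enrolled and informed about their allocation by a research assistant", and that "The first-line managers are not blinded to allocation since they will know about their participation in the problem-solving training" or, for controls, in the workshop.

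The employee exclusion criteria include bullying by the first-line manager. Employees who meet the inclusion criteria are told their screening result and "are recommended to talk to their first-line managers".

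Strengths and limitations describes screening by blinded assistants and concludes: "By using this procedure, we can reduce the risk of selection bias". It then concedes a risk that "only employees who have confidence in and a trustful relationship with their first-line manager will respond", so that mainly motivated employees, or those with minor problems, enter. The only consequence it draws concerns generalisability.

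**The concern.** Randomising managers makes the two groups of managers comparable. It makes the enrolled employees comparable only if entry to the trial does not depend on the arm. Here every step of entry follows allocation: answering the screen, reporting symptoms, reporting bullying by the manager, and consenting. The manager whose arm has been fixed is also the person whose relationship with the employee, on the article's own account, may decide who responds.

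If that relationship or the manager's behaviour differs by arm at the time of screening, the enrolled employees can differ in their expected sick leave before any intervention meeting takes place. The difference would be counted as an intervention effect, or would mask one. Register-based outcome data do not protect against this, because the problem lies in who is counted and not in how their days are measured.

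**Working it through.** **1. Who can influence each step of entry**

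- *Being sent the screen.* It goes to all employees of included managers (Recruitment of employees), so managers do not choose whom to approach. This route is closed.
- *Applying eligibility.* A blinded assistant applies fixed cut-offs to the answers (Eligibility criteria). The assessor's route is closed.
- *Knowing the arms.* Employees in both arms get the same information, without the content of the arms (Randomization and blinding). This limits, but does not remove, what an employee can learn from a manager who is not blinded.
- *Responding and disclosing.* Strengths and limitations itself links response to trust in the manager. No safeguard acts here.
- *The bullying exclusion.* It depends on what the employee reports about the manager, after allocation. No safeguard acts here.
- *Consenting.* It follows allocation. Employees who meet the inclusion criteria have been advised to talk to the manager, and the article does not say whether that conversation comes before or after consent and baseline.

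**2. Could the arms differ on what drives entry?** Intervention managers attend a 1½-day course with role-play and training in validating communication, which the article expects to build trust. Control managers attend a 3-hour lecture that also gives some communication advice. The arms therefore differ in how far they train the attribute said to drive response. This matters at screening only if managers already know their arm or have been trained by then. The article neither states nor excludes that. If training comes before baseline, the baseline leadership, influence and supervisor-support scores could be affected too.

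**3. The plan's own power figure.** Inputs from Statistical power: 19 clusters per arm of 3 employees (57 per arm), control mean 108 days, 30% difference, SD 60, intra-cluster correlation 0.015, two-sided 5% level.

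- Difference: 0.30 × 108 = 32.4 days.
- Design effect: 1 + (3 − 1) × 0.015 = 1.03.
- Standard error of the arm difference: 60 × √(2 × 1.03 / 57) = 11.4 days.
- Power (normal approximation): Φ(32.4/11.4 − 1.96) = 81%. The stated figure of about 80% is reproduced.

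**4. What a recruitment imbalance would do.** Let b be the difference in expected sick-leave days between arms caused by recruitment alone. The documents give no value, so b is assumed. SD and sample size are kept as above.

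- With no true effect, type I error = 1 − Φ(1.96 − b/11.4) + Φ(−1.96 − b/11.4).
- With a true effect of 32.4 days and an imbalance running against the intervention, power = Φ((32.4 − b)/11.4 − 1.96).

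| Assumed b (days) | b as share of 108 days | Type I error, no true effect | Power if b masks the effect |
|---|---|---|---|
| 0 | 0% | 5% | 81% |
| 5 | 4.6% | 7% | 67% |
| 10 | 9.3% | 14% | 50% |
| 15 | 13.9% | 26% | 33% |

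**The case against.** The strongest reply is that the harmful sequence is not actually written down. The article puts randomisation before screening, but gives no date for telling managers their arm or for the training, and the flowchart is not available in the text at hand. A reader might infer that trained managers are already at work when employees are screened, and that baseline scores are therefore post-intervention values. The documents do not support that as a fact. It is one sequence that the text leaves open, and the baseline point holds only if training comes first.

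The safeguards also deserve credit. Screening of all employees, fixed cut-offs applied by a blinded assistant, and identical information remove selection by managers and by assessors. Intervention managers are told to discuss the intervention only among themselves and with the project team; this is aimed at contamination, but it also limits what employees learn. The article claims only to reduce selection bias, and that is fair.

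The direction of any bias is unknown: better listening might attract milder cases, or bring more severe cases forward. A reader might also infer that selection alone could produce the whole 30% target effect. The documents give no enrolment or leave rates by arm from which to show that.

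Finally, register sick leave for the 24 months before baseline is collected (Primary outcome). It does not depend on how employees answer a questionnaire, and it allows an imbalance to be looked for and partly adjusted.

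All of this narrows the point without removing it. None of the safeguards governs how a manager who knows the arm affects response, disclosure or consent. Past leave cannot stand in fully for current symptoms or willingness to take part.

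**Conclusion.** The point holds as a design risk, not as demonstrated bias. Two things are certain from the text: employee recruitment follows the randomisation of a manager who is not blinded, and the article's discussion of trust-dependent response stops at generalisability when, with this order, it is also a matter of internal validity.

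The size is unknown and could go either way. The figures of 7%, 14% and 26% for type I error rest on assumed imbalances of 5, 10 and 15 days, on the plan's mean, SD and intra-cluster correlation being right, and on a normal approximation. They show that imbalances well below the 32.4-day target would matter at this sample size, not that they will occur. The stated sample size and power are not in question here.

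**What to change.** Within each company: enrol the managers; screen their employees, apply the exclusions, obtain consent and complete baseline; lock the participant list; then randomise the managers, stratified by company as planned. If managers must be randomised earlier, withhold the allocation from them and hold neither the training nor the lecture until the list is locked. State this order explicitly in the protocol.

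The change is one of scheduling and wording. The number of employees needed and the stated power stay the same, and managers with no eligible employee need not be randomised. The real cost is a delay between screening and intervention. The GHQ-12 asks about the past few weeks, so the wait should be kept short, for example by working company by company.

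If recruitment has already begun:

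- report the numbers screened, eligible and consented by arm;
- compare the arms on register sick leave over the 24 months before baseline, and adjust the primary analysis for it;
- state when managers were told their arm and trained, relative to screening and baseline;
- rewrite the paragraph on trust-dependent response in Strengths and limitations so that it names a threat to internal validity as well as to generalisability.
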